### 2.4. Randomization and Blinding

Sixty-four women over 60 years of age will be invited to participate in the study voluntarily and then will be electronically randomized [23] and assigned to either experimental group 1 (*n* = 16; adapted taekwondo: TKD), experimental group 2 (*n* = 16; multi-component training: MCT), experimental group 3 (*n* = 16, walking exercise: WE) or the control group (CG, *n* = 16; no intervention).

### 2.5. Participants

The participants will be recruited in the city of Talca (Maule region), Chile. The inclusion criteria for the sample will be: (i) older women aged between 60 and 65 years old; (ii) presenting the ability to understand and follow instructions in a contextualized way through simple commands; (iii) independent, that is, have a score equal to or greater than 43 points in the Preventive Medicine Exam for the Older People (in Spanish, EMPAM) of the Ministry of Health of Chile [24]; and (iv) complying with at least 85% attendance at the sessions scheduled for interventions. Regarding the exclusion criteria, the following will be considered: (i) having any disabling disease; (ii) those women who have musculoskeletal injuries or who are undergoing physical rehabilitation treatment that prevents their typical physical performance; and (iii) those who are permanently or temporarily unable to engage in physical activity. As depicted in Figure 1, all those who meet the inclusion criteria will be included in the study.

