## 1. Introduction

Scientific evidence has extensively documented the benefits of regular physical activity on various health variables in older people [1,2,3,4,5]. For example, a significant reduction in resting blood pressure and heart rate [4], lower incidence of cardiovascular events [6] and falls [1,2], a significant increase in cardiorespiratory fitness, muscular endurance and strength, flexibility, agility, and dynamic balance [7,8], as well as significant improvements in attention [9] and cognitive processing speed [10]. Facts that, as a whole, favor functional independence and improve health-related quality of life in older people [3,4].

Some of the most recurrent physical activity strategies to intervene in older people correspond to resistance training [1,5], multi-component training [7,11], and walking exercise [6,12], probably because they have greater diffusion, scientific support, and versatility to dose the magnitude of the load and the exercises to the characteristics of the participants [5,13]. Following the above, government-sponsored physical activity programs for older people have reported endurance, strength, flexibility, balance, agility, walking, healthy dancing, and recreational sports as the main activities. However, their average adherence rate reaches 50% [4].

In the same context, physical activity interventions for older people based on Olympic combat sports have reported a mean adherence greater than 80% [8,13,14], with similar physical, physiological, and psychoemotional outcomes to other physical activity intervention strategies such as those mentioned above (resistance training, multi-component training, and walking exercise). Specifically, interventions with adapted taekwondo in older people have reported a significant increase in muscle strength of the lower [9,15] and upper limbs [15], cardiorespiratory fitness [9], flexibility [9], agility and dynamic balance [9,15,16,17], as well as significant improvements in the multidirectional reach test and a significant decrease in the gait stability ratio [17]. Cho and Roh [9] reported a significant increase in brain-derived neurotrophic factor, vascular endothelial growth factor, and insulin-like growth factor-1, while Lee, Scott, Pekas, Lee, Lee and Park [15] reported a significant decrease in resting epinephrine. In summary, taekwondo improves the health status of older people with adherence rates greater than 90% through interventions lasting 11 to 16 weeks [9,15,16,17].

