### 2.6. Intervention

The TKD and MCT protocols will be distributed in three weekly sessions of 60 min on alternate days for 16-weeks (48 sessions). The general structure of the TKD and MCT protocols will include a 10 min warm-up consisting of joint mobility exercises and low-intensity aerobic work; then, for 40 min, the central part (TKD or MCT) will be developed to finish with a 10 min cool down through dynamic and static flexibility exercises. For their part, the WE protocol will be distributed in three weekly sessions of 45 to 60 min every other day for 16-weeks (48 sessions). A summary of the progression of all interventions is presented in Table 1.

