### 2.7. Outcomes and Procedures

The first meeting with the participants will be held to explain the scope and aim of the study, obtain the signature of informed consent, administer the anamnesis, and randomly assign them to the intervention groups. Next, for a week, the older women will be assessed on the variables considered for the study; later, they will participate in the designated training programs. After 16-weeks of intervention, older women will undergo the same initial assessments for one week. One of the researchers will supervise all the assessments, which will be carried out by an anthropometrist (body composition), a nurse (blood pressure, lipid profile, and frequency of food consumption), a speech-language pathologist (cognitive status and health-related quality of life), a psychologist specializing in neuroscience (brain activity), and two physical education teachers (physical-functional fitness). The evaluators will not have information about the training groups, nor will the participants know their identities (i.e., a double-blind shield). Figure 2 shows a summary of the assessments and sessions that are usually part of the intervention.

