#### 2.8.2. Analysis by Protocol

Only those volunteers who have completed more than 85% of the training sessions will be considered for this analysis. The same procedures as those indicated for intention-to-treat analysis will be conducted.

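### The 85% attendance rule is listed as an inclusion criterion, although it can be judged only after randomisation, and it contradicts the separate intention-to-treat and per-protocol analyses

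*Protocol article*

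**What the plan says.** Section 2.5 (Participants) gives four inclusion criteria. The first three (age, ability to follow instructions, functional independence) can be checked at entry. The fourth is "complying with at least 85% attendance at the sessions scheduled for interventions". The section ends by saying that "all those who meet the inclusion criteria will be included in the study".

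Section 2.7 (Outcomes and Procedures) describes the first meeting, at which the team will "obtain the signature of informed consent, administer the anamnesis, and randomly assign them to the intervention groups". The week of baseline assessments comes next, and training after that.

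Section 2.8.1 is headed as an intention-to-treat analysis and states no attendance condition. Section 2.8.2 defines a second analysis: "Only those volunteers who have completed more than 85% of the training sessions will be considered for this analysis". It adds: "The same procedures as those indicated for intention-to-treat analysis will be conducted".

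Section 2.6 schedules taekwondo and multi-component training as "three weekly sessions of 60 min on alternate days for 16-weeks (48 sessions" in total), and gives walking 48 sessions as well. Under section 2.6.4 the control group has the initial and final assessments and a weekly telephone call, but no sessions.

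**The concern.** Attendance over 16 weeks is an outcome of the assigned treatment and of how the woman responds to it. It is not a characteristic she brings to randomisation. Used as an eligibility rule, it makes membership of the sample depend on what happens after allocation. The groups being compared are then no longer the groups that were randomised.

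Two things are at stake:

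- **Which women are analysed.** A team that follows section 2.5 leaves out randomised women below the threshold. A team that follows the heading of section 2.8.1 keeps them. Both could claim to be following the protocol, and the choice could be made after the data are seen.
- **Whether the comparison is still randomised.** Under section 2.5, each training arm would be reduced to its adherent members. The control arm has no attendance to select on, so adherent trainees would be compared with unselected controls. The comparison of taekwondo with the other two programmes, which is the trial's main question, would also be between groups selected by behaviour under different treatments.

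**Working it through.** **Inputs from the protocol article:** 3 sessions a week for 16 weeks in each training arm (2.6); attendance of at least 85% for inclusion (2.5); more than 85% for the per-protocol analysis (2.8.2); 16 women per group and 64 in all (2.4); randomisation at the first meeting (2.7).

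**Step 1: the number of sessions.** 3 × 16 = 48, which agrees with the stated total.

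**Step 2: the threshold in sessions.** 0.85 × 48 = 40.8. Since 40/48 = 83.3% and 41/48 = 85.4%, a rule of at least 85% means 41 or more sessions. A rule of more than 85% also means 41 or more, because no whole number of sessions gives exactly 85%. The different wording in 2.5 and 2.8.2 therefore makes no difference, and the two rules are the same.

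**Step 3: when the criterion can be judged.** A woman may miss at most 48 − 41 = 7 sessions. At three a week, the 41st session falls in week 14 (13 × 3 = 39; 14 × 3 = 42), so nobody can be shown to meet the criterion before then. The earliest possible failure is at the 8th missed session, in week 3 (2 × 3 = 6; 3 × 3 = 9). Both are after randomisation.

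**Step 4: the analysis sets under each reading.**

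| | Criterion (iv) applied as written | Criterion (iv) not applied |
|---|---|---|
| Intention-to-treat set, training arms | women with 41 or more sessions | all 16 per arm |
| Per-protocol set, training arms | women with 41 or more sessions | women with 41 or more sessions |
| Controls | no scheduled sessions, so the rule has no meaning | all 16 in intention-to-treat; entry to the per-protocol set not stated |

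In the first column the two training-arm sets are identical, and section 2.8.2 repeats 2.8.1. Only in the second column do the two sections describe different analyses. Sections 2.5, 2.8.1 and 2.8.2 therefore cannot all stand.

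**Step 5: can the size be estimated?** That would need the share of women in each arm who reach 41 sessions, and how their outcomes differ from those of the others. The document gives neither. The Introduction says of government programmes that "their average adherence rate reaches 50" per cent, and that "taekwondo improves the health status of older people with adherence rates greater than 90" per cent. These are background averages and do not fix the share above a threshold. For example, assume an arm of 16 with mean attendance of 50%: it logs 16 × 24 = 384 sessions, and 384/41 = 9.4, so up to 9 of the 16 women could still reach 41 sessions.

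**The case against.** The strongest reply is that the authors did not mean to remove anyone. No section says that a randomised woman below 85% is withdrawn, left unassessed or dropped from 2.8.1. Section 2.8.2 limits its filter to that analysis, and a separate intention-to-treat section makes sense only if women with low attendance stay in it. Section 2.7 plans the final assessments without an attendance condition. On this reading, item (iv) is a misplaced line. This much stands: removal is a consequence of applying 2.5 literally, not a stated procedure. It does not make the text consistent, because item (iv) speaks of complying, and nothing recasts it as willingness to attend.

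Three stronger readings are tempting, and the document does not support them:

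- **That no control could be enrolled or analysed.** Sections 2.4 and 2.6.4 plainly allocate 16 controls and assess them twice. What remains is that 2.8.2 does not say how controls enter the per-protocol set. Alone, that is a detail that an analysis plan could supply.
- **That the protocol forecasts different adherence by arm.** The 50% is an average for mixed government programmes, and the figure above 90% comes from published taekwondo studies. Activity and setting both differ, and neither figure is a forecast for this trial's supervised arms. Differential selection is possible but not predicted.
- **That most women in a poorly attended arm would be lost.** The bound of 9 of 16 in step 5 shows that this does not follow from a mean of 50%.

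**Conclusion.** The point holds as a contradiction between section 2.5 and sections 2.8.1 and 2.8.2. An eligibility criterion depends on behaviour after randomisation, and its threshold is the same as the per-protocol threshold: 41 of 48 sessions. If it is applied as written, women with 40 or fewer sessions fall outside the sample, the two analysis sets coincide in all three training arms, and those arms are selected on adherence while the control arm is not. That would bias the comparison by an amount the document does not allow one to estimate.

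The 41-session threshold and the identity of the two sets follow from the protocol's own figures. The bias depends on the criterion actually being applied, which the document leaves open. It should be settled before any outcome data are analysed, because it decides which women enter every comparison.

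**What to change.** - Delete item (iv) from the inclusion criteria in section 2.5.
- State in 2.8.1 that the intention-to-treat analysis includes all 64 randomised women in their assigned group, whatever their attendance.
- Keep the 85% rule only in 2.8.2, for the three training arms, and say there how controls enter the per-protocol set, for example by completing both assessments.

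The cost is one deletion and about two sentences, with no change to the number of women or to the assessments. The downside is that the estimated effect may be slightly smaller, because non-adherent women stay in the main analysis.

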### 2.6. Intervention

The TKD and MCT protocols will be distributed in three weekly sessions of 60 min on alternate days for 16-weeks (48 sessions). The general structure of the TKD and MCT protocols will include a 10 min warm-up consisting of joint mobility exercises and low-intensity aerobic work; then, for 40 min, the central part (TKD or MCT) will be developed to finish with a 10 min cool down through dynamic and static flexibility exercises. For their part, the WE protocol will be distributed in three weekly sessions of 45 to 60 min every other day for 16-weeks (48 sessions). A summary of the progression of all interventions is presented in Table 1.

#### 2.6.1. Adapted Taekwondo (TKD) Program

The main part of the TKD program will consist of non-contact activities, distributed in 10 min of basic postures and specific movements with the upper limbs (strikes and blocks) and 20 min of lower limb movements (displacement, postures, kicks) performed individually and in pairs with and without the implementation of taekwondo (shields and impact pads). In addition, choreographies or poomsae (sequence of arm and leg movements that simulate imaginary combat) specific to this modality were adapted to the characteristics of older women for 10 min. The training volume will be quantified by sets and the number of repetitions of the specific movements (i.e., strikes, blocks, displacement, postures, and kicks) with the rest of 2 min between sets. The intensity of the training takes into account the recommendations of previous studies with older people [9,15], so it will remain moderate to vigorous using the percentage of the maximum heart rate (HRmax) of each participant for its control (between 50% and 70% of the HRmax) with a heart rate sensor strap (H10, Polar Electro Oy, Kempele, Finland), which will be live transmitted throughout the protocols (TKD, MCT, and WE) through Bluetooth to a tablet (iPad 4, Apple, Inc., Cupertino, CA, USA) where the participants will be continuously monitored using the Polar Team app version 1.3 (Polar Electro Oy, Kempele, Finland). The rating of perceived exertion will be measured with the Borg scale (maximum value of 10 points). The adapted taekwondo sessions will be led by a Ph.D. student in health and certified as a taekwondo instructor by the National Sports Federation of Taekwondo WT. The sessions will take place in the multipurpose room of gym B of the Universidad Católica del Maule, which has an EVA rubber floor (tatami).

#### 2.6.2. Multi-Component Training (MCT) Program

The main part of the MCT will consist of 40 min of distributed work in a circuit, including resistance training focused on the large muscles of the upper limbs (i.e., biceps, triceps, deltoids, and latissimus dorsi) and lower limbs (i.e., quadriceps, hamstrings, glutes, and gastrocnemius) combined with exercises aimed at cardiorespiratory fitness, agility and postural control (static and dynamic balance), using elastic bands, poles, 2-kg medicine balls, and chairs, following previous recommendations [4,5,7,11,22]. The training volume will start (the first 4-weeks) with 3 sets of 10 repetitions per muscular exercise with a 2 min rest period between the sets, performing slow movements of two seconds in concentric contraction and four seconds in eccentric contraction [25]. Between weeks 5 to 8, the volume will increase to 4 sets of 10 repetitions per muscular exercise with 2 min of rest between sets. Between weeks 9 and 12, the sets will remain at 4, and the number of repetitions will be increased to 12; finally, between weeks 13 and 16, the number of sets and repetitions (4 × 12) will be maintained reducing the rest time to 90 s. The resistance training intensity will be moderate to vigorous (between 5 to 8 points), controlled with the OMNI-Resistance Exercise Scale of perceived exertion [26]. The intensity of the cardiorespiratory fitness, agility, and postural control will be maintained at moderate to vigorous (between 50% and 70% of the HRmax), controlled with a heart rate sensor strap (H10, Polar Electro Oy, Kempele, Finland), which will be live transmitted through Bluetooth to a tablet (iPad 4, Apple, Inc., Cupertino, CA, USA), and individualized according to the initial assessments of the participants and following previous recommendations [3,5]. Furthermore, the rating of perceived exertion will be used (Borg scale of 10 points). The MCT sessions will be directed by a Master’s student in physical activity sciences with experience working with older people. The sessions will take place in the multipurpose room of gym B of the Universidad Católica del Maule, which has an EVA rubber floor (tatami).

#### 2.6.3. Walking Exercise (WE) Program

The general structure of the WE program will include a 5 min warm-up consisting of joint mobility and flexibility exercises. Next, the main part will be developed for 30 to 45 min (increased by 5 min every 4-weeks), consisting of walking on flat ground, touring the university’s jogging circuit, and ending with 5 min cool down through dynamic and static flexibility exercises. The training volume will be regulated by the distance traveled using triaxial accelerometers (ActiGraph GT9X, Pensacola, FL, USA), and the intensity will be kept at moderate to vigorous (between 50% and 70% of the HRmax) controlled with a heart rate sensor strap (H10, Polar Electro Oy, Kempele, Finland), which will be live transmitted through Bluetooth to a tablet (iPad 4, Apple, Inc., Cupertino, CA, USA). The progression of the load will be adjusted every 4-weeks, increasing the walk by 5 min and regulating the cadence individually, which will increase the distance covered by the participants—the rating of perceived exertion (Borg scale of 10 points). The design of the WE considers recommendations and previous studies [3,6,12]. A Master’s student in physical activity sciences with experience working with older people will lead the walking sessions.

#### 2.6.4. Control Group (CG)

Regarding the CG, the individuals will participate in the assessments (initial and final) and will be asked to maintain their usual activities of daily living. A research assistant will contact the participants by telephone (once a week) to inquire about their health status and monitor their activities. At the end of the intervention period, the CG will be invited to participate in a physical activity program developed at the University based on the results of this study.

### 2.7. Outcomes and Procedures

The first meeting with the participants will be held to explain the scope and aim of the study, obtain the signature of informed consent, administer the anamnesis, and randomly assign them to the intervention groups. Next, for a week, the older women will be assessed on the variables considered for the study; later, they will participate in the designated training programs. After 16-weeks of intervention, older women will undergo the same initial assessments for one week. One of the researchers will supervise all the assessments, which will be carried out by an anthropometrist (body composition), a nurse (blood pressure, lipid profile, and frequency of food consumption), a speech-language pathologist (cognitive status and health-related quality of life), a psychologist specializing in neuroscience (brain activity), and two physical education teachers (physical-functional fitness). The evaluators will not have information about the training groups, nor will the participants know their identities (i.e., a double-blind shield). Figure 2 shows a summary of the assessments and sessions that are usually part of the intervention.

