## 2. Material and Methods

### 2.1. Study Design

The study includes an experimental design (randomized controlled trial), double-blind, repeated measures, four parallel groups (three interventions and one control), and a quantitative approach. The methodology followed will be the Consolidated Standards of Reporting Trials Statement (CONSORT) methodology [21].

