#### 2.8.1. Intention-to-Treat Analysis

A two-factor repeated measures ANOVA will be used to determine the effects of the intervention on the outcomes (group × time). Post-hoc tests will be performed with an alpha adjusted by Bonferroni to identify statistically significant differences. The effect sizes will be calculated utilizing Cohen’s d [35] within the group and between the groups, using the following equation: effect sizes = (post mean − pre mean)/standard deviation combined. The level of significance will be set at 5%. The intraclass correlation coefficient will be used to verify the measurement’s reliability, with a predetermined threshold of 0.80 being used to include the data in the analyses. The inter-individual variability of the intervention will be determined using previously reported criteria, and responders and non-responders will be classified using the technical error (TE) of measurement. This TE will be calculated according to the formula: TE = SD (standard deviation) dif/√2, where SD is the variance of the differences in the observed values of two repeated measurements in each test [36]. A non-responder is a person who does not show an increase or decrease (in favor of beneficial changes) in the study variable greater than twice the TE, far from zero. Thus, a shift in favor of beneficial health effects, which is <2 TE means the existence of a high probability (12 to 1 odds ratio) that the response to exercise is true [36,37]. In addition, Fisher’s exact test will compare groups of participants who were at 2 × TE calculated on each outcome as non-responders and more than twice the TE as responders [37].

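### Women are randomised before the baseline week, and the plan describes no concealment of the arm until effort-dependent and self-reported baselines are complete

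*Protocol article*

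**What the plan says.** Section 2.7 of the protocol article has the study explained and consent signed at the first meeting, and then continues: "administer the anamnesis, and randomly assign them to the intervention groups. Next, for a week, the older women will be assessed". Training comes only after that week: "Next, for a week, the older women will be assessed on the variables considered for the study; later, they will participate in the designated training". Section 2.4 does not set a different order. It says only "Sixty-four women over 60 years of age will be invited to participate in the study voluntarily and then will be electronically randomized", with no timing relative to baseline. Figures 1 and 2 are not available in the text reviewed.

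On blinding, Section 2.1 describes the design as "experimental design (randomized controlled trial), double-blind, repeated measures, four parallel groups (three interventions and one control". Section 2.7 adds "The evaluators will not have information about the training groups, nor will the participants know their identities (i.e., a double-blind shield". The control group, under Section 2.6.4, "will participate in the assessments (initial and final) and will be asked to maintain their usual activities of daily living".

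On analysis, Section 2.8.1 states "A two-factor repeated measures ANOVA will be used to determine the effects of the intervention on the outcomes", through the group × time term. It defines effect size as post mean minus pre mean over a combined SD, and it classes each woman as responder or non-responder by comparing her change with twice the technical error.

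**The concern.** A baseline measured before allocation cannot be affected by it. A baseline measured afterwards can be, if the woman knows which arm she is in. Someone just told that she will do taekwondo, a circuit, walking or no training may try harder or less hard on a chair stand, or answer the SF-36 differently.

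The planned analysis makes this matter, because the baseline value is part of every quantity reported: the group × time term, the effect size and the individual change behind responder status. The outcomes named in the hypotheses (cognitive status, brain activity, quality of life, postural balance) rest largely on self-report or on the woman's cooperation with a task.

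There is a second consequence. A woman who leaves during the assessment week has been randomised but has no baseline, and the analysis labelled intention-to-treat needs both time points.

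**Working it through.** **1. Order of events.** From Section 2.7: consent, anamnesis, random assignment, one week of baseline assessment, training, final assessment. Section 2.4 does not contradict this.

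**2. What is said about knowledge of the arm.** Evaluators are stated to have no group information. The clause on participants says that they will not know certain identities, and does not make clear whether this means their own arm. No time of disclosure is given. Participants cannot remain blind once training starts, so any blinding of participants could only cover the baseline week, and the article does not describe it as doing so.

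**3. How a shift enters the estimate.** Let knowledge of the arm move one arm's mean by s_pre at baseline and s_post at week 16, relative to a comparator.

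- Bias in the change contrast (group × time) = s_post − s_pre.
- If the reaction is the same at both times, the bias is 0.
- If it has gone by week 16, the bias is −s_pre.
- If half persists, the bias is −s_pre/2.
- With baseline adjustment instead, at pre-post correlation ρ and equal variances, the bias is s_post − ρ·s_pre. For s_pre = 1 and s_post = 0 this is 0.5 in size at ρ = 0.5 and 0.9 at ρ = 0.9, so adjustment reduces the problem but does not remove it.

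**4. Illustration on the chair stand.** Inputs from Section 2.3: difference 3.46 repetitions, SD 3.38, 16 per group, 15% loss. The planning effect is 3.46/3.38 = 1.02 SD. The stated 16 is reproduced by a paired two-sided t test: n = 13, and 13/0.85 = 15.3, rounded up to 16. This point does not dispute that figure. After loss, 16 × 0.85 = 13.6, so 13 per arm is shown as well.

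Assumptions not in the document: the net shift b (the part of the baseline shift not present at week 16) and ρ between 0.5 and 0.9. With no true effect and a two-sided 5% t test of change between two arms, the SD of change is 3.38·√(2(1−ρ)) and the noncentrality is b/(SD of change·√(2/n)).

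| Net shift b (repetitions) | In SD | Share of 3.46 | Rejection rate, 16 per arm (ρ 0.5 to 0.9) | Rejection rate, 13 per arm (ρ 0.5 to 0.9) |
|---|---|---|---|---|
| 0 | 0 | 0% | 5% | 5% |
| 0.5 | 0.15 | 14% | 7% to 15% | 6.5% to 13% |
| 1 | 0.30 | 29% | 13% to 44% | 11% to 37% |
| 2 | 0.59 | 58% | 37% to 95% | 31% to 90% |

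The first row applies if the arm is concealed until baseline is complete, if the outcome does not respond to knowledge of the arm, or if the reaction persists unchanged.

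**5. Direction.** Enthusiasm that raises the taekwondo baseline and then fades reduces the measured taekwondo gain. Disappointment that lowers the control baseline and then fades enlarges the control gain. Both work against taekwondo. A lower baseline effort in the taekwondo arm would work the other way. The document does not determine which applies.

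**6. Which outcomes.** The mechanism reaches the Senior Fitness Test, handgrip, reaction-time and cognitive tasks, the SF-36 and the food survey. It does not plausibly reach lipids by meter, anthropometry or bioimpedance, and hardly reaches automated blood pressure.

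**7. Withdrawal in the baseline week.** Each such woman is 1/16 = 6% of an arm. Without a pre value she cannot enter a two-time-point repeated-measures ANOVA.

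**The case against.** The strongest reply is that the article says when women are assigned, not when they are told, and that it calls the trial double-blind. If the arm is withheld through the baseline week, the bias is zero. A condensed article may also leave the time of disclosure to the full protocol. This stands to the extent that a reader might infer that baseline is collected with the arm known, and the document does not say so. It does not remove the point. The order itself is a stated procedure, and the only sentence that could protect it is unclear.

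Three further limits are accepted.

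- A reader might infer that every pre-post comparison is biased. The mechanism is motivation and self-report, and several outcomes are instrument readings taken by evaluators said to be blind.
- A reader might infer that the baseline week lets evaluators learn the arm. Section 2.7 says that they have no group information, and nothing contradicts it.
- A reader might infer that the order favours taekwondo. The most natural reactions would shrink its apparent benefit. Disappointment in the control group also does not enter the hypothesised contrasts, which compare taekwondo with multi-component training and walking.

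Finally, a reaction that lasts to week 16 cancels wholly or partly in the change score, so the bias need not equal the full baseline shift.

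**Conclusion.** The point holds in a conditional form. Baseline follows randomisation, and the plan describes no concealment of the arm from the women until baseline is complete. If they know their arm, effort-dependent and self-reported baselines can be shifted, and the part of the shift not also present at week 16 passes into the group × time estimate, the effect sizes and the responder classification.

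The size cannot be known from the document. The chair-stand figures rest on an assumed net shift and an assumed correlation, and do not carry over to other outcomes. The direction is open and may be against taekwondo. The loss of women who withdraw in that week from the intention-to-treat analysis follows from the stated order alone, whatever they know about their arm.

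It is worth correcting before enrolment, because analysis cannot fully repair a baseline that allocation has influenced.

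**What to change.** Reorder Section 2.7: consent, anamnesis and eligibility check; the one-week baseline assessment; then electronic randomisation, with the group disclosed just before session 1. Align Figure 2 if it shows the present order.

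If the order cannot be changed, state that the arm is withheld from the women, and from the evaluators as already intended, until baseline is complete.

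In either case, rewrite the double-blind sentence to say who is blind, to what and until when, since participants cannot be blind once training begins.

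The cost is moving one step by about a week, with the same staff and assessments. The group has to be communicated after baseline and not at the first meeting.
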